This study is designed to measure the impact of the Simple Intervention and Comprehensive Intervention on the number of women and infants tested and identified as HIV-positive as well as the percentage uptake of certain immunizations. Statistical power calculations are based on the immunization uptake outcome variable, as this is the indicator with the smallest effect size required to be policy-relevant. The study will test the following null hypotheses:

- - 1. Infants are not less likely to attend immunization clinics for DPT1, OPV1, DPT2 and OPV2 immunizations in Comprehensive Intervention health facilities versus the combination of the Simple Intervention and Comparison health facilities
    2. Rapid HIV antibody tests are not more likely to be administered in:
       1. Simple Intervention facilities versus Comparison facilities
       2. Comprehensive Intervention facilities versus Simple Intervention facilities
    3. DNA PCR tests are not more likely to be administered in:
       1. Simple Intervention facilities versus Comparison facilities
       2. Comprehensive Intervention facilities versus Simple Intervention facilities
    4. Mothers are not more likely to be identified as HIV-positive in:
       1. Simple Intervention facilities versus Comparison facilities
       2. Comprehensive Intervention facilities versus Simple Intervention facilities

Below are the power calculation for each of the outcomes we intend to measure:

*Effect of Comprehensive Intervention on immunization rates*

- **Level of outcome:** DPT 1 immunization
- **Sample:**
  - 20 Comprehensive Intervention facilities compared to 40 Simple Intervention and Comparison facilities
  - 98 new infants per facility
- **Detectable percentage point decrease in immunization uptake:** 10%
- **95% plausibility interval:** Expected probability that an infant receives DPT1 immunization is 87% with bounds around this estimate from 55 – 95%
- **Significance level:** 5%
- **Power:** 86%^[[29]](#footnote-7)^

*Effect of Simple Intervention on rapid HIV antibody testing rates (Simple versus Comparison facilities)*

- **Level of outcome:** Rapid HIV antibody tests administered
- **Sample:**
  - 20 Simple Intervention facilities compared to 20 Comparison facilities
  - 98 new infants per facility
- **Detectable percentage point increase in antibody tests:** 5%

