- **95% plausibility interval:** Expected probability that a mother/infant pair receives a rapid HIV antibody test is 5% with bounds around this estimate from 1 - 10%
- **Significance level:** 5%
- **Power:** 87%

*Effect of Comprehensive Intervention on rapid HIV antibody testing rates (Comprehensive versus Simple facilities)*

- **Level of outcome:** Rapid HIV antibody tests administered
- **Sample:**
  - 20 Comprehensive Intervention facilities compared to 20 Simple Intervention facilities.
  - 98 new infants per facility
- **Detectable percentage point increase in antibody tests:** 20%
- **95% plausibility interval:** Expected probability that a mother/infant pair receives a rapid HIV antibody test is 15% with bounds around this estimate from 1 - 30%^[[30]](#footnote-8)^
- **Significance level:** 5%
- **Power:** 93%

*Effect of Simple Intervention on DBS PCR testing rates (Simple versus Comparison facilities)*

- **Level of outcome:** DBS PCR tests administered
- **Sample:**
  - 20 Simple Intervention facilities compared to 20 Comparison facilities
  - 98 new infants per facility
- **Detectable percentage point increase in DBS PCR tests:** 4%
- **95% plausibility interval:** Expected probability that an infant pair receives a DBS PCR test is 5%^[[31]](#footnote-9)^ with bounds around this estimate from 1 - 10%
- **Significance level:** 5%
- **Power:** 75%^[[32]](#footnote-10)^

*Effect of Comprehensive Intervention on DBS PCR test rates (Comprehensive versus Simple facilities)*

- **Level of outcome:** DBS PCR tests administered
- **Sample:**
  - 20 Comprehensive Intervention facilities compared to 20 Simple Intervention facilities
  - 98 new infants per facility
- **Detectable percentage point increase in DBS PCR tests:** 4%
- **95% plausibility interval:** Expected probability that a mother/infant pair receives a DBS PCR test is 9% with bounds around this estimate from 5 - 14%^[[33]](#footnote-11)^
- **Significance level:** 5%
- **Power:** 82%

*Effect of Simple Intervention on percentage of new mothers identified as HIV-positive (Simple versus Comparison facilities)*

- **Level of outcome:** HIV-positive mothers identified
- **Sample:**
  - 20 Simple Intervention facilities compared to 20 Comparison facilities.
  - 98 mother / infants pairs per facility
- **Detectable percentage point increase in HIV-positive mothers identified:** 0.8%

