28. First immunizations refer to the 6-week visit for under-five health facility where children receive the following vaccinations: OPV1 and DPT1-HepB-HiB. The Second immunization refers to the 10-week visit to under-five health facility for OPV2 and DPT2 vaccines. [↑](#footnote-ref-6)
29. Analysis will include the use of historical immunization data as covariates which will increase power to a level greater than 80%. For the sample frame, at least 60 to 70% of the variation in immunization rates on a month to month basis can be explained by the previous year of data. [↑](#footnote-ref-7)
30. This assumes that the simple intervention will have the effect assumed in the previous power calculation because this calculation compares comprehensive clinics to simple clinics. [↑](#footnote-ref-8)
31. This assumes that of the approximately 45,000 babies tested currently for a DNA PCR, around two-thirds are first test PCR (done at around the 6-week time frame) and the remaining 1/3 are retests. This means that 30,000 out 600,000 babies born each year receive a PCR test at 6 weeks - around 5%. [↑](#footnote-ref-9)
32. As in the case of the immunization data, covariates will be used to increase power for this outcome [↑](#footnote-ref-10)
33. This assumes that the simple intervention will have the effect assumed in the previous power calculation because this calculation compares comprehensive clinics to simple clinics. [↑](#footnote-ref-11)
34. A linear regression measuring the effect of the Comprehensive Intervention on immunization uptake will be used to assess any decrease in immunizations. “Confirmed” indicates a drop of 20 percentage points is observed at a 95% confidence level. [↑](#footnote-ref-12)
35. National Protocol Guidelines, Integrated Prevention of Mother-to-Child Transmission of HIV/AID in Zambia, 2008 Page 8. [↑](#endnote-ref-23)

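### The Comprehensive v Simple antibody power starts Simple facilities at 15%, but its own footnote 30 and the preceding step imply 10%; the stated 93% rests on the 15%.

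*Protocol*

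**What the plan says.** Sample Size and Justification gives two linked calculations for rapid antibody testing.

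- **Simple versus Comparison.** The Comparison rate is given as "Expected probability that a mother/infant pair receives a rapid HIV antibody test is 5% with bounds around this estimate from 1 - 10" (percent). The effect is "Detectable percentage point increase in antibody tests: 5" (percent), and the stated power is 87%.
- **Comprehensive versus Simple.** The starting rate is given as "Expected probability that a mother/infant pair receives a rapid HIV antibody test is 15% with bounds around this estimate from 1 - 30" (percent). The effect is "Detectable percentage point increase in antibody tests: 20" (percent), and the stated power is 93%. The sample is "20 Comprehensive Intervention facilities compared to 20 Simple Intervention facilities", with "98 new infants per facility".

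Footnote 30, attached to the 15% line, links the two: "This assumes that the simple intervention will have the effect assumed in the previous power calculation". Footnote 33 says the same for the PCR step.

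**The concern.** If the second step carries forward the Simple effect of the first, Simple facilities start at 5% + 5 points = 10%. The protocol starts them at 15%. The same facilities therefore have two expected testing rates in adjacent calculations, and the footnote that should explain the second rate contradicts it.

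Antibody testing is a listed primary outcome, and Comprehensive versus Simple is one of its two named hypotheses. What is at stake is whether a stated planning rate, and the power and detectable increase attached to it, can be relied on.

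**Working it through.** **1. Do the chains add up?**

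| Outcome | Comparison rate + Simple effect | Implied Simple rate | Simple rate used in the next step |
|---|---|---|---|
| PCR test | 5% + 4 points | 9% | 9% |
| HIV-positive mothers | 0.2% + 0.8 points | 1.0% | 1.0% |
| Antibody test | 5% + 5 points | 10% | **15%** |

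Only the antibody chain breaks.

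**2. Reproducing the stated powers.** The protocol prints no formula, so this one is inferred from its results. It works on the logit scale.

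- Between-facility SD from the plausibility bounds: τ = [logit(upper) − logit(lower)] / (2 × 1.96)
- Effect: g = logit(p₂) − logit(p₁)
- Variance: V = Σ over both arms of [τ² + 1/(n·p(1 − p))] / J, with J = 20 facilities per arm and n = 98
- Power: noncentral F with 1 and 38 df, noncentrality g²/V, two-sided 5%

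The protocol does not say whether the 5% is one- or two-sided; two-sided fits (one-sided would give 96.9% where 93% is stated).

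For 15% to 35% (the 35% is 15 + 20 and is not printed), bounds 1–30%:
- τ = (−0.847 + 4.595) / 3.92 = 0.956, so τ² = 0.914
- g = −0.619 + 1.735 = 1.116
- V = (2 × 0.914 + 0.045 + 0.080) / 20 = 0.0977
- g/√V = 3.57, power **93.6%** (stated 93%)

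The same formula gives the other five HIV-related powers within about 1 point:

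| Calculation | Recomputed | Stated |
|---|---|---|
| Antibody, Simple v Comparison | 88.1% | 87% |
| PCR, Simple v Comparison | 75.0% | 75% |
| PCR, Comprehensive v Simple | 83.0% | 82% |
| HIV-positive, Simple v Comparison | 76.9% | 76% |
| HIV-positive, Comprehensive v Simple | 87.5% | 87% |

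It does not match the immunization power (91.4% against the stated 86%), so the match is claimed only for the HIV calculations.

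**3. Starting from 10%, bounds kept at 1–30%.**
- 10% to 30%: g = −0.847 + 2.197 = 1.350; V = (1.828 + 0.049 + 0.113) / 20 = 0.0995; g/√V = 4.28; power **98.6%**
- 10% to 25%: g = 1.099; g/√V = 3.48; power **92.3%**. An increase of about 15 points thus has roughly the power stated for 20.
- 10% to 35% (keeping the implied end point): 99.8%

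None of the 20-point or larger increases from 10% gives 93%, so the 93% was computed from 15%.

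**4. Which effect was used in the preceding step?** With bounds 1–10%, τ² = 0.374. From 5% to 10% the power is 88.1%, close to the stated 87%. From 5% to 15% it is 99.9%. The 5-point effect was the one used there, and it was not carried forward.

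**5. Sensitivity to the bounds.** The 1–30% bounds were set around 15% and would need restating around 10%. For 10% to 30%, with assumed bounds:

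| Assumed bounds | Power |
|---|---|
| 0.5–30% | 94.5% |
| 1–40% | 96.4% |
| 1–35% | 97.7% |
| 1–30% | 98.6% |
| 1–25% | 99.3% |
| 1–20% | 99.8% |

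**The case against.** The strongest reply is that nothing in the design depends on this. The correction raises power, the section calls its power figures lower bounds, and it says the power calculations are based on immunization uptake. All of that stands. A reader might infer that the comparison is underpowered or that the 60 facilities are in doubt; the figures show the opposite.

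A second reply is that 15% may be a free-standing assumption. It lies close to the midpoint of its own bounds, and footnotes 30 and 33 are worded alike, so footnote 30 could have been copied across. That is possible and the protocol does not settle it. It follows that 15% cannot simply be called the wrong number. It does not remove the contradiction, because footnote 30 as printed denies that 15% is free-standing.

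Third, 93% is correct for the inputs printed beside it. That also stands: the fault is in the starting rate's agreement with its footnote, not in the power computation.

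A reader might also infer that the mismatch distorts test-kit quantities, the yield of newly identified HIV-positive mothers, or the cost model. The documents do not support this. Supply reinforcement gives no kit number or formula, and the budget line for backup tests is a lump sum without derivation. The HIV-positive calculations use their own rates. Data Analysis bases at-scale costs on external inputs and cost estimates from the evaluation.

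**Conclusion.** The contradiction holds. Footnote 30 and the preceding step put Simple at 10%, the calculation uses 15%, and the stated 93% is reproduced from the 15%. With a 10% start, the same 20-point increase and bounds of 1–30%, power is about 98.6%; equivalently, about 15 points is detectable with about 92% power. The error is in the safe direction: no sample size, hypothesis or analysis changes.

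This rests on an inferred formula, which matches all six HIV-related powers within about 1 point, and on keeping the bounds at 1–30%. A fixed floor such as 98% should not be read into it, since the bounds must be restated and plausible choices move the power between 94.5% and 99.8%. The protocol also leaves open whether the slip lies in the 15%, the preceding 5-point effect or footnote 30, although the preceding 87% shows that 5 points was used there.

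**What to change.** Reconcile the starting rate with footnote 30 in one of three ways:

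1. Set Simple to 10%, restate its plausibility bounds, and recompute either the power for the 20-point increase (about 98.6% if the bounds stay at 1–30%) or the detectable increase.
2. If Simple is expected to reach 15%, change the Simple versus Comparison effect to 10 points and recompute that power (99.9% with its present bounds, in place of 87%).
3. If 15% is a separate assumption, correct footnote 30 and give the reason for 15%.

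The cost is a small text correction: one input and its power figure, or one footnote with a justification. The design and the 60 facilities stay as they are.

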- **95% plausibility interval:** Expected probability that a mother is identified as HIV-positive is 0.2% with bounds around this estimate from 0.1 – 1.0%
- **Significance level:** 5%
- **Power:** 76%

*Effect of Comprehensive Intervention on percentage of new mothers identified as HIV-positive (Comprehensive versus Simple facilities)*

- **Level of outcome:** HIV-positive mothers identified
- **Sample:**
  - 20 Comprehensive Intervention facilities compared to 20 Simple Intervention facilities
  - 98 mother/infant pairs per facility
- **Detectable percentage point increase in HIV-positive mothers identified:** 1.5%
- **95% plausibility interval:** Expected probability that a mother is identified as HIV-positive is 1.0% with bounds around this estimate from 0.5% – 2.0%
- **Significance level:** 5%
- **Power:** 87%

These power calculations represent lower bounds, as covariate analysis will further increase the actual power of the evaluation. We can assume that because all research questions are sufficiently powered to detect effects between either the comprehensive and simple facilities or the simple facilities and the comparison facilities, all research questions are sufficiently powered to evaluate effects between the comprehensive and comparison clinics in the case where the simple clinics show no effect.

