There is a low risk of John Henry effect, the process in an evaluation by which the comparison group realizes that it is a comparison group and changes its behavior in response. Patients are unlikely to realize they are in comparison catchment areas and change their behavior in any way other than outlined in the spillover section. There exists a risk that comparison facilities could take steps to improve EID services that they would not have done in the absence of the evaluation. The research team will attempt to measure this by comparing EID testing rates from before the intervention with testing rates during the evaluation.

There is a low risk of any survey effects for this evaluation. No surveys with durations of over 30 minutes at a time are expected. Because the main outcomes are directly observed, not asked of the respondents, any survey effects are likely to be minimal.

*Site Attrition*

All sites included in the randomization will have appropriate infrastructure and staffing levels to participate in the study. Thus, it is unlikely that facilities will drop out from the study due to inability to implement the intervention. Because unexpected changes to staffing levels may still lead to attrition, additional facilities have been included in the sample size calculations to ensure adequate statistical power in the event of such occurrence.

*Patient attrition*

Patient-level attrition could manifest itself due to incorrect facility register recordings. This will be minimized through training and regular monitoring of facility health staff on proper register data collection. Respondent attrition is possible for those who do not consent to exit interviews. However, these activities are not central to the core analysis.

Bounds analysis will be used to account for any attrition in the ultimate analysis.

*Impact heterogeneity*

Facility registers provide important baseline data on HIV testing, EID, and EPI services and other patient characteristics. Additional baseline information on facility staff, equipment and buildings will be collected. This information will allow the study team to calculate whether the intervention had a differential impact across important variables.

Ethical Issues

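### The two DBS PCR power figures (75% and 82%) rest on different between-clinic variances for the same 20 Simple clinics; no single assumption gives both, and unadjusted Comprehensive versus Simple power runs from about 45% to 87%

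*Protocol*

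**What the plan says.** The protocol's Sample Size and Justification section gives two linked calculations for DBS PCR tests.

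- **Step 1, Simple versus Comparison:** "20 Simple Intervention facilities compared to 20 Comparison facilities", "98 new infants per facility", a detectable rise of 4 points, "Significance level: 5" percent. The base rate reads "Expected probability that an infant pair receives a DBS PCR test is 5" percent, with bounds of 1 to 10%. Stated power: 75%.
- **Step 2, Comprehensive versus Simple:** "20 Comprehensive Intervention facilities compared to 20 Simple Intervention facilities", with the same cluster size, rise and significance level. The base rate reads "Expected probability that a mother/infant pair receives a DBS PCR test is 9% with bounds around this estimate from 5 - 14" percent. Stated power: 82%.

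Footnote 33 says that step 2 carries forward the effect assumed for the Simple arm. It says nothing about clinics becoming more alike. The section closes with "These power calculations represent lower bounds, as covariate analysis will further increase the actual power of the evaluation". Under Site Attrition the protocol adds that "additional facilities have been included in the sample size calculations to ensure adequate statistical power in the event of such occurrence". Data Analysis names the logit regression as primary.

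**The concern.** The step 2 interval is the step 1 interval moved up by exactly 4 points. In percentage points the spread looks unchanged (9 points wide in both). On the log-odds scale it is much narrower, because the same width further from zero is a smaller relative spread. The Simple clinics appear in both calculations, so the two steps describe the same clinics with different variability and give no reason.

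EID testing of HIV-exposed infants is the first primary objective, and Comprehensive versus Simple for DNA PCR is a named hypothesis. It tests whether integration adds anything to supplies and reminders. A null result would be read against a believed 82% power. The protocol also rests its claim of adequate power for Comprehensive versus Comparison on these figures.

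**Working it through.** **Formula.** The protocol gives no formula, variance or sidedness, so these are inferred. With lower and upper bounds L and U:

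- Between-clinic variance: tau = [(logit U − logit L)/3.92]².
- Variance of the difference in log-odds: the sum over the two arms of [tau + 1/(98·p(1−p))]/20.
- Power: noncentral F with 1 and 38 degrees of freedom, two-sided 5%.

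**Variances.**

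- Bounds 1–10%: [(−2.197 + 4.595)/3.92]² = 0.374.
- Bounds 5–14%: [(−1.815 + 2.944)/3.92]² = 0.083.
- Ratio: 4.5.

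**Reproducing the stated powers** (bounds applied to both arms):

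| Outcome | Step | Recomputed | Stated |
|---|---|---|---|
| Antibody test, 5→10% | 1 | 88.1% | 87% |
| Antibody test, 15→35% | 2 | 93.6% | 93% |
| DBS PCR, 5→9% | 1 | 75.0% | 75% |
| DBS PCR, 9→13% | 2 | 83.0% | 82% |
| HIV-positive mothers, 0.2→1.0% | 1 | 76.9% | 76% |
| HIV-positive mothers, 1.0→2.5% | 2 | 87.5% | 87% |

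The same formula misses DPT1 (20 versus 40 clinics): 91% against 86% stated. A one-sided test gives 84% and 90% for the two DBS steps, which fits neither. Equal spread on the percentage scale (9/3.92 = 2.3 points in every arm) gives 95% and 88%, which also fits neither.

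**DBS step 2 at the step 1 variance.**

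- Log-odds difference: −1.901 + 2.314 = 0.413.
- Within-clinic terms: 1/(98 × 0.09 × 0.91) = 0.125 and 1/(98 × 0.13 × 0.87) = 0.090.
- Variance: (0.374 + 0.125)/20 + (0.374 + 0.090)/20 = 0.048, so the SE is 0.2195.
- Noncentrality: 0.413/0.2195 = 1.88. Power: 45% (facility-level simulation 43–44%).

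**DBS powers under each treatment of the Simple clinics:**

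| Assumption | Simple v Comparison | Comprehensive v Simple |
|---|---|---|
| 0.374 in every arm | 75% | 45% |
| 0.083 in every arm | 97% | 83% |
| Uniform 4-point rise, arm-specific variances (Comparison 0.374, Simple 0.083, Comprehensive 0.041 from 9–18%) | 87% | 87% |
| Simple keeps 0.374, Comprehensive 0.083 | – | 59% |
| As stated | 75% | 82% |

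**Covariates.** Suppose, as an assumption, that covariates explain 50%, 60% or 70% of a between-clinic variance of 0.374. Step 2 power is then 65%, 71% or 77%. About 74% must be explained to reach 80%.

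**Other outcomes.** The variance implied by the bounds rises between steps for antibody tests (0.374 to 0.914) and falls for HIV-positive mothers (0.348 to 0.128). At the step 1 variance, step 2 power goes from 93% to over 99% for antibody tests and from 87% to 79% for HIV-positive mothers.

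**Spare facilities.** The protocol calls 60 facilities, 20 per group, the required number, and every calculation uses all of them. At 18 per arm, Simple versus Comparison falls from 75% to 70% for DBS and from 76% to 72% for HIV-positive mothers.

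**The case against.** The strongest defence is that the two intervals describe different clinic states: 1–10% surrounds the Comparison rate, and 5–14% the Simple rate after its assumed gain. Effects are given in percentage points, and a uniform 4-point rise moves the interval exactly as printed. On that reading 82% is conservative. This stands, and it rules out saying that 82% is false. It does not rescue the pair, because step 1 would then have about 87% power, not 75%.

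A reader might infer that the true step 2 power is 45%. The documents do not support that. The figure places the variance of untreated clinics on both treated arms, and it is before the planned adjustment for historical EID rates. Footnote 32 invokes covariates to raise power for the DBS outcome. The one figure given for variance explained, 60–70% in footnote 29, concerns immunization rates, so using it here is an assumption.

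Two further objections hold. A consistent variance does not make every power worse, since antibody power rises. The formula is inferred, and it misses DPT1.

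On spare facilities, the protocol may have meant headroom above 80% on DPT1, where the formula still gives 88% at 18 versus 36. That cannot apply to outcomes stated at 75% and 76%.

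**Conclusion.** The inconsistency holds; a fixed corrected power does not. The stated 75%/82% follows from no single treatment of the Simple clinics. Unadjusted power for Comprehensive versus Simple on DBS PCR runs from about 45% to 87%, depending on an assumption that the protocol does not state.

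This rests on an inferred formula. Six matches within about 1 point, and its agreement with the scale of the primary analysis, make the inference good but not certain.

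The lower-bound claim is fair only in the sense of before covariate adjustment, and only if the variance used is right. The statement that additional facilities are in the calculations contradicts the sample size section. This should be fixed, but it changes no facility count, estimate or analysis.

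**What to change.** 1. State the between-clinic variance behind each HIV power, its scale, the formula and the sidedness of the test.
2. For every HIV outcome, use one justified assumption for the Simple clinics in both steps, ideally from prior-year register data. Antibody power will rise. Power for HIV-positive mothers, Comprehensive versus Simple, falls from 87% to 79% if the step 1 variance is kept.
3. Restate the DBS powers as a consistent pair or a range. Do not print 75%/45% as fixed values unless data support 0.374 in every arm.
4. Limit the lower-bound sentence to power before covariate adjustment, conditional on the stated variance.
5. Replace the Site Attrition sentence: all 60 facilities are used, so none is spare. Give power at 18 per arm (Simple versus Comparison: 70% for DBS, 72% for HIV-positive mothers).

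The cost is recalculation, a summary of existing register data and wording. No facilities are added. Some stated powers may become less favourable.

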Sinunu et al. (2011) ran a study in Malawi to determine the mother-to-child transmission rate in the country ahead of the adoption of Option B+. The research team utilized a random selection process to select a sample of mother-infant pairs attending immunizations to test for HIV-exposure. They found that 9.8% of mother’s tested positive who had never tested before, 6.9% of women who tested negative before pregnancy were now HIV-positive, and 4% of women who tested negative since pregnancy were now HIV-positive. The overall prevalence rate for mothers was 14.4% with 8.4% of positive mothers passing HIV onto their infant.^[[19]](#endnote-18)^

*Provider Initiated Testing and Counseling (PITC)*

A study in Lilongwe, Malawi, used a pre- post comparison to find that implementation of provider-initiated HIV testing and counseling, and integration of ART services in the pediatric ward, was associated with an increase in uptake of testing services and number of patients initiated on ART. The proportion of children and adults initiating ART each quarter increased from 26% to 53%, and 20% to 52%, respectively.^[[20]](#endnote-19)^

In Zambia, a study at primary care outpatient health facilities in Lusaka, Zambia, found that introducing routine PITC significantly increased the uptake and acceptability of HIV testing. After the addition of PITC, the nine health facilities in the sample group tested over twice as many patients as before. Over time, the percentage of individuals who accepted testing rose, indicating that introducing PITC helped to decrease the stigma surrounding HIV testing.^[[21]](#endnote-20)^

*Medical Benefits of Early Identification and Treatments of HIV-Positive Children*A randomized trial conducted by the National Institutes of Health found benefits to early infant initiation of ART, instead of waiting to initiate treatment until disease symptoms are seen. This is especially important since HIV disease progression occurs more rapidly in infants than in adults. In the study, early identification of HIV status and early initiation of antiretroviral therapy reduced early infant mortality by 76%.^^[[22]](#endnote-21)^^

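### The 0.8-point effect behind the 76% power for HIV-positive mothers identified (Simple versus Comparison) does not fit the protocol's own testing increase

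*Protocol*

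**What the plan says.** All the planning figures are in the Protocol, Sample Size and Justification.

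- **Identification, Simple versus Comparison.** The design is "20 Simple Intervention facilities compared to 20 Comparison facilities", with "98 mother / infants pairs per facility". The baseline reads "Expected probability that a mother is identified as HIV-positive is 0.2" per cent, with an interval of 0.1% to 1.0%. The effect is "Detectable percentage point increase in HIV-positive mothers identified: 0.8" points, at 5% significance and 76% power.
- **Antibody testing, same two arms.** "Expected probability that a mother/infant pair receives a rapid HIV antibody test is 5" per cent, with a detectable increase of 5 points.
- **Antibody testing, Comprehensive versus Simple.** The expected rate is now 15%, with a 20-point increase. A footnote says this assumes the Simple effect from the preceding calculation.
- **Identification, Comprehensive versus Simple.** "Expected probability that a mother is identified as HIV-positive is 1.0" per cent, with a 1.5-point increase and 87% power.

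The section closes by calling the calculations lower bounds, because covariates will add power. It treats all research questions as sufficiently powered and extends this to Comprehensive versus Comparison.

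The Literature Review cites a Malawi study of mothers at immunization visits. Positivity was 9.8% in women never tested and 6.9% in women negative before pregnancy, and "4% of women who tested negative since pregnancy were now HIV-positive". Overall maternal prevalence was 14.4%. The protocol states no positivity for the extra women its interventions would test.

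**The concern.** A woman is newly identified by being tested, so the two Simple versus Comparison lines are linked. One has testing double (5% to 10%). The other has identification rise fivefold (0.2% to 1.0%). Both can hold only if the extra tests yield positives at four times the baseline rate.

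Both increases are labelled detectable, but the 0.8 points does not stay a mere detectable difference. The next line takes 0.2% + 0.8% = 1.0% as the expected Simple-arm rate, so it becomes the base of the 87% figure.

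Identification of HIV-positive women is a primary outcome, and Simple versus Comparison is one of the listed hypotheses. If the contrast is presented as adequately powered when the planned testing increase would give a much smaller effect, a null result could be taken by the ministries as evidence that the Simple Intervention finds no more HIV-positive mothers.

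**Working it through.** **Inputs (Protocol, Sample Size and Justification).** 20 versus 20 facilities and 98 pairs per facility, so 1,960 per arm. Baseline 0.2%, interval 0.1% to 1.0%, 5% significance. Sidedness is not stated; two-sided is used because it reproduces the stated power.

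**Step 1: reproduce the 76%.** Work on the log-odds scale and take the between-facility variance from the plausibility interval:

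- τ² = [(logit 0.010 − logit 0.001)/3.92]² = (2.312/3.92)² = 0.348
- Var(log OR) = Σ over arms of [τ² + 1/(98·p·(1−p))]/20 = (0.348 + 5.112 + 0.348 + 1.031)/20 = 0.342
- log OR = 1.617, and 1.617/√0.342 = 2.77
- Non-central F(1, 38), two-sided 5%: **76.9%**, against the stated 76%

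The same formula gives 88.1%, 93.5%, 75.1%, 83.0% and 87.5% for the other five 20-versus-20 lines (stated 87%, 93%, 75%, 82%, 87%). The 93% is matched by 15% to 35%; 10% to 30% would give 98.6%. The formula does not reproduce the DPT1 line (20 versus 40 facilities: 91% against 86%), which is not used here. A one-sided test would give 85.8% for the line at issue.

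**Step 2: positivity implied by the planning figures.**

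- Baseline: 0.2/5 = 4%
- Extra tests, testing 5% to 10%: 0.8/5 = **16%**
- Extra tests, testing 5% to 15%: 0.8/10 = **8%**
- Simple arm in the later lines: 1.0/15 = 6.7%
- Comprehensive step: 1.5/20 = 7.5%

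**Step 3: power when identification follows from testing.** Simple-arm rate = 0.2% + (extra testing × positivity). For example, 5 points at 4% gives 0.4%: log OR 0.695, variance (0.695 + 5.112 + 2.561)/20 = 0.418, ratio 1.075, power 18.2%.

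| Positivity in extra tests | +5 points: rate, power | +10 points: rate, power |
|---|---|---|
| 4% | 0.40%, 18% | 0.60%, 42% |
| 6.9% | 0.545%, 35% | 0.89%, 70% |
| 9.8% | 0.69%, 52% | 1.18%, 85% |
| 14.4% | 0.92%, 72% | 1.64%, 95% |

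At 0.2% versus 0.4% the expected counts are 1,960 × 0.002 = 3.9 and 1,960 × 0.004 = 7.8 women per arm.

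**Step 4: check by another method.** Facility proportions were simulated with the same between-facility variance and compared by a t test. Power was 89% for 0.2% to 1.0%, 48% for 0.2% to 0.6%, and 19% for 0.2% to 0.4%. The level depends on the method; the steep fall does not.

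**Step 5: Comprehensive versus Simple, at 4% positivity and the stated 20-point testing step.** Each range uses the two between-facility variances that the protocol's intervals imply (0.348 from 0.1% to 1.0%; 0.128 from 0.5% to 2.0%).

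- Testing 10% to 30%: 0.4% to 1.2%, power 66% to 71%
- Testing 15% to 35%: 0.6% to 1.4%, power 56% to 62%

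The stated figure is 87%.

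**The case against.** **The 76% is not a miscalculation.** This stands. It is right for 0.2% to 1.0%; the fault lies in how the inputs fit together.

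**The protocol also gives 15% as the Simple testing rate.** This stands and limits the point. A reader might infer that power is simply 18%, or that the protocol's testing rates cannot produce the assumed effect. Neither is supported. On 15% the required positivity is 8%, which lies between the Malawi figures of 6.9% and 9.8%, and power at 9.8% is 85%. The 18% is the lowest corner of the range. But 15% contradicts its own footnote, since 5% plus the preceding 5-point effect is 10%.

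**The 4% is not a stated assumption.** Correct: it is the ratio 0.2/5. The later lines imply 6.7% to 7.5%, and women of unknown status may test positive more often than women negative since pregnancy. At 6.7% to 7.5%, however, 5 extra points still give only 34% to 39%.

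**Covariates will add power.** They help little here. At 0.2% versus 0.4%, binomial noise supplies 5.112 + 2.561 = 7.67 of the 8.37 in the variance numerator. Ignoring clustering altogether gives about 21%.

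**The facility number does not rest on this line.** Also correct: the protocol says its power calculations are based on immunization uptake. What is affected is the stated power and the blanket assurance, not the size of the trial.

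**Conclusion.** The point holds as a conflict between planning assumptions. At the testing increase stated for this contrast, the 0.8-point effect needs 16% positivity, above every maternal figure the protocol cites; at the alternative 15% testing rate it needs 8%. Over positivity of 4% to 9.8%, power is about 18% to 52% with 5 extra points of testing and about 42% to 85% with 10, against the stated 76%. Until the two testing rates are reconciled, no single figure can replace the 76%.

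These results assume that additional identifications come only through additional antibody tests, that testing and identification share the 98 pairs per facility as denominator (as the power section has it), that the plausibility interval describes between-facility spread, and that the test is two-sided. The positivity range is borrowed from the Malawi study and is not a protocol assumption.

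**What to change.** 1. Reconcile the Simple-arm testing rate: 10% (5% plus 5 points) or 15%, with the footnote made to agree.
2. State the positivity assumed among the extra women tested, with 4% to 9.8% as the range.
3. Derive the identification rates from the testing rates, and restate the Simple versus Comparison power as the resulting range.
4. Recompute Comprehensive versus Simple from the same inputs, instead of starting from 1.0%.
5. Withdraw the sentence that all research questions are sufficiently powered, and its extension to Comprehensive versus Comparison, unless the reconciled inputs support it.
6. State that a null Simple versus Comparison result on this outcome will be reported with its confidence interval and not read as no effect.

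This needs no extra facilities and no change to data collection. The only cost is less favourable stated power.
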